**Primary outcome**				
	Medication adherence to statins	Urine test	✓	✓
**Secondary outcomes**				
	Cardiovascular disease risk score (%)	QRISK2 calculator	✓	✓
	TC^c^, HDL^d^, TC:HDL (mmol/L)	Blood sample	✓	✓
	Blood pressure (mm Hg)	Omron monitor	✓	✓
	Body mass index (kg/m^2^)	Height (cm) and weight (kg)	✓ (height and weight)	✓ (weight only)
	Smoking history	Self-report using QRISK2 format	✓	✓
	Fruit and vegetable intake	Self-report: 5-a-day Community Evaluation Tool (FACET) [38]	✓	✓
	Quality of life	Self-report: 15D (a generic, comprehensive, 15-dimensional, standardized measure of health-related quality of life) [39]	✓	✓
	Health status	Self-report: EuroQol 5 dimensions questionnaire (EQ-5D, a standardized instrument for measuring generic health status) [40]	✓	✓
	Physical activity	Self-report: International Physical Activity Questionnaire (IPAQ; short form) [41]	✓	✓
	Patient activation	Self-report: Patient Activation Measure (PAM, a valid and reliable scale that reflects a developmental model of an individual’s readiness for health behavior change) [42]	✓	✓
	Medication/Health Beliefs	Self-report: Beliefs about Medicines Questionnaire (BMQ) [43] and the Brief Illness Perception Questionnaire (Brief IPQ) [44]	✓	✓
	Medication adherence to statins	Self-report: 8-item Morisky Medication Adherence Scale (MMAS)^f^ [37]	✓	✓
**Other supporting outcomes^e^**				
	Prescription history	Record of repeat prescription issues for statins and antihypertensives (if applicable) from the GP database	✓	✓
	Adverse events	Self-report and observed from GP database	✓	✓

^a^N/A: not applicable.

^b^GP: general practitioner.

^c^TC: total cholesterol.

^d^HDL: high-density lipoprotein.

^e^For the duration of the study.

^f^Use of the MMAS is protected by US and International copyright laws. Permission for use is required. A license agreement is available from: [name], MMAS Research (MORISKY), [name]; [contact].

In addition, the self-reported 8-item Morisky Medication Adherence Scale (MMAS) was completed at baseline and 12 months. This is an established and validated scale that is commonly used to measure adherence [37,50,51]. At the end of the study, we asked GP practices to provide details for individual participants regarding both statin and antihypertensive (if applicable) prescription issued during the 12 months of the study (Table 1). These data will provide useful supporting information about the pattern of patient medication adherence behavior over the 12-month study period.

#### Secondary Outcomes

Secondary outcomes were adherence to antihypertensive medications and other anticipated potential effects of the intervention, including a change in overall CVD risk score measured by the QRISK2 calculator [52], as well as potential changes in the following individual CVD risk factors: total cholesterol, high-density lipoprotein, total cholesterol to high-density lipoprotein ratio, blood pressure, and body mass index. We also observed changes in behavior and lifestyle using validated questionnaire measures: smoking, physical activity, fruit and vegetable intake, patient activation level, well-being, health status, health and medication beliefs, and medication adherence to antihypertensives (for participants prescribed this treatment for high blood pressure). We collected all outcome measures at the baseline and 12-month clinics in line with standard operating procedures and good clinical practice guidelines (Table 1). In addition, we checked for and recorded adverse events at the final visit and whenever a participant was contacted, for the purpose of the study, to monitor health status during the course of the study. Table 1 details all outcome data collected at the specified time points.

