### Study Design

The study was an open, individual, and pragmatic randomized controlled trial recruiting participants from UK general practices (attached to a single study center). We recruited patients identified as being at high risk of CVD for primary prevention (total cholesterol ≥5 mmol/L) and already prescribed statins to reduce this risk. Participants were randomly assigned to either the control group (usual GP care) or the intervention group (3R Group Education Program plus follow-up telephone and SMS text messaging support). For both the control and intervention participants, the GP was informed of a patient’s participation in the study but was not made aware of their group allocation. Both groups attended clinic visits at baseline and 12 months so that we could collect outcome data at these time points (Figure 1).

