**Figure 1 figure1:**
[figure not shown]
Study design. CVD: cardiovascular disease; GP: general practitioner.

Reply slips (from both positive and negative responders) were returned directly to the research team. We contacted all positive responders to verbally screen and confirm their eligibility for the study. Following this, eligible patients who were interested in taking part were booked to attend an initial data collection clinic. All participants were required to attend 2 data collection clinics: at baseline and at 12 months. The clinics were held in a suitable local venue, usually a community venue. Group clinics (of up to 8 participants at a time) were run by 3 trained study staff, including a qualified nurse. A full patient information sheet was sent with the clinic appointment letter. At the baseline clinic, written informed consent for all participants was taken by a trained research nurse before the collection of any data. All participants were made aware that they could withdraw from the study at any time. For each participant, a blood sample and clinical measurements were taken in accordance with local standard operating procedures, and a urine sample was collected. A hardcopy questionnaire booklet was completed at clinic by each participant. In addition, a hardcopy clinical research form was used to enter all other data collected at the baseline and 12-month time points, including demographic data, medical and medication histories, clinical measurements, blood results, and adverse events. Following clinics, all hardcopy study data collected were treated as confidential and kept securely in locked cabinets. Study data were anonymized and participants were identified by an allocated study number. These hardcopy data were then manually entered onto a validated, secure, and password-protected electronic database to be checked and verified prior to analysis.

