Ready to Reduce Risk (3R) Education Program.Setting: local venue (eg, community hall).Format: group education (approximately 8 per group; participants were allowed to take a partner or friend) facilitated by a written structured curriculum and mixed-media educational resources (including a free pedometer).Frequency: 2 sessions.Duration: approximately 2 hours each.Facilitators: 2 trained facilitators (at least one was a health care professional).Training: 2-day course, self-study, and practice run.Monitoring: ad hoc filmed sessions.OutlineSession 1: explored understanding and beliefs to do with cardiovascular disease risk and how to manage it; showed how to calculate their own risk score using the Joint British Societies calculator; raised awareness of factors that influence risk, how these affect the body, and the role of medication; and explored beliefs about medication adherence.Session 2: increased knowledge and awareness about how to have a healthier lifestyle to reduce cardiovascular disease risk and introduced behavioral control techniques to support activated participants.Theories and models: capability, opportunity, and motivation model; patient empowerment; working alliance; patient activation; self-regulation; self-determination; cognitive dissonance; self-efficacy.Behavioral control techniques: goal setting (outcome); problem solving; action planning; self-monitoring of outcome(s) of behavior; social support (emotional); social support (practical); information about health consequences; salience of consequences; demonstration of behavior; pros and cons; adding objects to the environment; incompatible beliefs; valued self-identity.

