Follow-up support phone calls after the Ready to Reduce Risk (3R) Education Program.Setting: participants were called at home by a member of the 3R study team from a private office and designated study mobile.Format: participants received individual calls facilitated by a semistructured script and delivered using a patient-centered approach.Frequency: 2 calls at approximately 2 weeks and 6 months.Duration: approximately 10-20 minutes each.Facilitator: a trained member of the 3R team who was experienced in calling research participants.Monitoring: written records of the calls were documented by the facilitator, using a structured template.Outline: participants were called at a convenient time and asked some questions about how they were getting on following the 3R Education Program. The facilitator used open questions to elicit information about what had been going well and not so well, and participants were given the opportunity to discuss any pitfalls and ways to overcome these.Theories and models: the theoretical basis was the same as that for the 3R Education Program.Behavioral control techniques: goal setting (outcome); problem solving; action planning; self-monitoring of outcome(s) of behavior; social support (emotional); social support (practical); information about health consequences; pros and cons; valued self-identity.

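### Adverse events are recorded at every study contact, and only the intervention arm has scheduled contacts between clinics, so a tabulation by arm that includes those self-reports leans toward more events in that arm

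*Protocol article*

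**What the plan says.** The rule for collecting adverse events is in the protocol article under Secondary Outcomes: "we checked for and recorded adverse events at the final visit and whenever a participant was contacted, for the purpose of the study". The stated aim is to monitor health during the study.

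Scheduled contact differs by arm:

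- **Both arms.** Study Design: "Both groups attended clinic visits at baseline and 12 months so that we could collect outcome data at these time points". According to Method of Recruitment, the clinical research form completed at these clinics covers data "including demographic data, medical and medication histories, clinical measurements, blood results, and adverse events".
- **Intervention arm only.** The textbox on the education program gives "Frequency: 2 sessions", and the textbox on support calls gives "2 calls at approximately 2 weeks and 6 months". The text messages are one-way, so they offer no chance to report an event.
- **Control arm.** Usual GP care and a mailed booklet, which both arms received. No scheduled two-way contact between the clinics is described.

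Table 1 places adverse events under the other supporting outcomes. The source is "Self-report and observed from GP database", with the footnote "For the duration of the study", and the arms are not distinguished. Study Design and Randomization both state that GPs were not told the allocation.

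**The concern.** When recording is triggered by contact and contact depends on allocation, the chance that an event is recorded depends on the arm. The extra contacts are also of a kind likely to bring events out. The calls ask openly what has gone badly as well as what has gone well, and the first session deals with the role of medication and beliefs about adherence. The trial is open, and the calls are made by the study team.

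What is at stake is how the safety data are read. The intervention aims to increase statin taking, so a true rise in statin-related complaints is possible. Additional reporting opportunities push the count in the same direction. If the sources are not kept apart, an excess in the intervention arm could be read as harm when it is only better capture, or a real increase could be dismissed as reporting bias.

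**Working it through.** The article gives no adverse event rate and no capture probability, so there is no planned figure to reproduce. The contact count comes from the text. The sizes below rest on assumed inputs.

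**Step 1: scheduled two-way contacts between the clinics.** Intervention: 2 sessions + 2 calls = 4. Control: 0. Adding the final visit gives at most 5 collection points after baseline against 1.

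**Step 2: self-report only, by time of event.** Assume each later contact captures the event independently with probability 0.20, calls are timed from the education program, attendance is complete and the GP record captures nothing. With k contacts remaining, capture = 1 − 0.8^k.

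| Event occurs | k, intervention | Intervention | Control (k = 1) |
|---|---|---|---|
| Before session 1 | 5 | 1 − 0.8^5 = 67% | 20% |
| After education, before first call | 3 | 1 − 0.8^3 = 49% | 20% |
| Between the two calls | 2 | 1 − 0.8^2 = 36% | 20% |
| After the 6-month call | 1 | 20% | 20% |

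**Step 3: average over the year.** Texts start 1 week after education and run for 44 weeks, so to fit in 52 weeks education must end by week 52 − 44 − 1 = 7. Take both sessions at week 2 or at week 7, calls 2 and 26 weeks later, and events spread evenly over 52 weeks:

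- Week 2: (2 × 0.672 + 2 × 0.488 + 24 × 0.36 + 24 × 0.20) / 52 = 15.76 / 52 = 30%.
- Week 7: (7 × 0.672 + 2 × 0.488 + 24 × 0.36 + 19 × 0.20) / 52 = 18.12 / 52 = 35%.

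The control value is 20% in both cases.

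**Step 4: add the GP record.** Let g be the probability that the GP record captures the event, independently of the other sources. For the event just after education, intervention capture is 1 − 0.8^3 (1 − g) and control capture is 1 − 0.8 (1 − g).

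| g | Intervention | Control | Ratio |
|---|---|---|---|
| 0 | 0.488 | 0.200 | 2.44 |
| 0.3 | 0.642 | 0.440 | 1.46 |
| 0.6 | 0.795 | 0.680 | 1.17 |
| 0.9 | 0.949 | 0.920 | 1.03 |
| 1 | 1.000 | 1.000 | 1.00 |

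**Step 5: vary the capture assumptions.** Let r be recall at the final visit (0.5 to 0.8) and c the total capture at interim contacts (0.3 to 0.7). Control capture is 1 − (1 − r)(1 − g) and intervention capture is 1 − (1 − r)(1 − g)(1 − c). With equal true risk, the apparent risk ratio is:

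| g | Apparent ratio |
|---|---|
| 0 | 1.08 to 1.70 |
| 0.3 | 1.05 to 1.38 |
| 0.6 | 1.03 to 1.18 |
| 0.9 | 1.01 to 1.04 |
| 1 | 1.00 |

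The direction is never reversed. The size depends almost entirely on how many events the sources common to both arms already capture.

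**The case against.** The strongest reply is that the article announces no analysis of the kind criticised. Adverse events are a supporting outcome, Statistical Methods specifies models only for the primary and secondary outcomes, and the stated reason for asking at each contact is participant monitoring. Nothing says that the sources are combined into one count. Source labels and table layout are details that an article commonly leaves to the full protocol or analysis plan. All of this stands, and it rules out calling the point an analysis error. It does not remove the point, because the unequal collection follows from a rule that the article itself states.

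A reader might infer that every between-arm comparison of adverse events is biased or cannot be interpreted. The documents do not support that. The 12-month visit and the GP record covering the study period are common to both arms, and GPs were not told the allocation. A comparison limited to these avoids the direct effect of the extra contacts.

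A reader might also take 67% against 20% as the size of the problem. That figure applies only to an event before session 1 that the GP record cannot capture. An event caused by better adherence after the program cannot occur that early.

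**Conclusion.** The point holds as a reporting risk. If a table by arm includes self-reports from sessions or calls, it is biased toward more recorded events in the intervention arm, mainly for minor or transient events that never reach the GP record. The firm part is the count of 4 scheduled interim contacts against 0. The size is unknown. Under the 20% assumption with no GP capture, it runs from 49% against 20% just after education to no difference after the 6-month call. It shrinks to nothing as GP capture approaches 100%. These sizes assume independent capture, full attendance and equal true risk.

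The article states neither pooling nor a test between arms, and the primary outcome is untouched. Asking about health at every contact is not itself at fault. This is a cheap improvement to make before the safety data are tabulated.

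**What to change.** Label each recorded event with its source: GP record, 12-month visit, education session, support call or other contact. Base any between-arm comparison on the GP record for the study period and the 12-month visit. List events learnt only at sessions or calls separately for the intervention arm, without comparison, and explain in a footnote why they are set apart. An event found both at a call and in a common source stays in the comparison.

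This needs no new data. The Results section says that analysis had not begun. Calls were documented on a structured template and all attempts were logged, so events learnt by telephone should be traceable. The article does not say whether events raised at group sessions can be traced in the same way, and this should be checked.

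The cost is a source label and fewer events in the comparative table. Some indirect difference may remain, because the program could change how readily participants consult their GP or what they recall at 12 months. The report should say so.

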#### Process Outcomes

We also collected process outcomes relating to participant acceptability and fidelity of the education intervention. We used feedback data from the evaluation forms given out following the end of the education sessions to assess participant acceptability in conjunction with retention rates for the 2 sessions. We videotaped 3 sessions, with the participants’ permission, to assess the fidelity of the delivered education sessions. Logs were kept to record the initiation, delivery, and any terminations of text messages, and all attempted follow-up support phone calls were recorded.

### Sample Size

The primary outcome measure was medication adherence to statins at 12 months. We based the sample size calculation on the percentage of nonadherers by using data from the Investigation of Text Message Reminders on Adherence to Cardiac Treatment (INTERACT) trial [32]. To detect a difference in the proportion of medication adherers (of 16 percentage points in the intervention group at 12 months compared with the usual-care control group—ie, 91% compared with 74%), we required 84 participants per group with 80% power and 5% significance. After allowing for a 20% dropout, we required 105 participants per group, making 210 participants in total. This minimum difference was based on a similar 16 percentage–point increase in adherence to cardiovascular preventive treatment observed in the INTERACT trial [32], which used text messaging as the sole intervention. This was a 6-month follow-up study with a final control group adherence of 75%. We envisaged similar adherence to medication at 12 months’ follow-up, following our complex intervention with continued follow-up support via SMS text messaging and phone calls to sustain any initial intervention effect.

The study design was pragmatic and reflected how it would be delivered if it were implemented in practice. The study was designed to mitigate the effects of unbalanced clustering in the intervention group by using a standardized curriculum, a small group of trained facilitators to deliver education and phone calls, a small number of venues, standardized text messages, and standardized phone calls. Moreover, we assessed process outcomes relating to fidelity to allow for clear reporting of any variation that occurred. This was in line with the Medical Research Council guidance for complex interventions [26].

### Statistical Methods

For evaluation, we will summarize baseline characteristics of the 2 groups with means, standard deviations, and medians and ranges for continuous variables; and counts and percentages for categorical variables. Logistic regression will assess the difference in medication adherence by group, adjusted for the stratification factors (sex and age) at 12 months. We will assess the primary outcome at the 5% level with 95% confidence intervals. The primary analysis at 12 months will be based on complete data. The analysis of the secondary outcomes will be conducted in a similar manner using the appropriate model type: logistic regression for binary outcomes, linear for continuous outcomes, and ordinal for ordinal outcomes.

We will carry out sensitivity analyses on an intention-to-treat basis and a per-protocol basis to examine robustness of conclusions for missing data and attendance of the program. To adhere to the intention-to-treat principle, we will impute missing outcome data by multiple imputation using the command MI in Stata (StataCorp LLC). We will also conduct analysis by adding the MMAS adherence data where urine adherence data are missing.

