### Randomization

Following confirmation of an eligible blood result for cholesterol, participants were randomly assigned at a 1:1 frequency by a trained member of the 3R team not involved with data collection, using an online randomization tool (Sealed Envelope Ltd, London, UK). Participants were stratified by age (40-53 years and 54-74 years) and sex before been randomly allocated to either the control or intervention group. If 2 people were taking part from the same household, they were automatically assigned to the same arm to prevent any contamination between groups taking place. We considered contamination between intervention and control participants from the same GP practice to be minimal based on evidence from a systematic review of contamination in trials of education interventions [24]. Although the intervention involved some fact giving, the main objective was motivation for behavior change and knowledge empowerment, which must be directly experienced to be effective and is therefore unlikely to result in contamination.

Following enrollment, blinding of participants was not possible due to the open and pragmatic design of the study. However, we took some steps to reduce bias: data were collected by research nurses not involved in any analysis; GPs were not informed of a participant’s group allocation; urine samples were analyzed by laboratory staff blinded to the randomized groups; and, prior to study completion, detailed protocol information was not made available online, which participants could have accessed.

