### Outcomes and Measures

#### Primary Outcome

The primary outcome was medication adherence to statins at 12 months (Table 1) [37-44]. The primary measure was a urine-based biochemical measure involving a novel assay to test for statin and antihypertensive levels in urine samples. This method has already been used successfully to show poor adherence to antihypertensive medication [45]. Participants were informed that urine samples would be collected to assess the levels of statins and were asked to provide a first morning urine sample (in a standard urine collection tube) prior to clinic. This test uses a high-performance liquid chromatography–tandem mass spectrometry analysis of spot urine samples (2-5 mL) to detect 60 commonly prescribed cardiovascular medications, including statins. The results are reported as binary outcomes (yes or no) and hence are based on the limit of detection of a medication. The limit of detection is in the low nanomolar per liter range for all medications (in-house data). The method has been set up using established laboratory criteria for qualitative assays [46]. The method is robust and reliable and has been developed from techniques used in forensic medicine [47] and in testing for drug abuse in elite sports [48]. We use the test routinely in various cardiovascular clinics, and have set up the first National Centre for Drug Adherence Testing and receive samples from 25 centers across the United Kingdom [49].

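### The outcome models adjust for sex and age but not for the outcome's own baseline value, although it was collected; the cost is power, not validity

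*Protocol article*

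**What the plan says.** For the primary outcome, the protocol article (Statistical Methods) states: "Logistic regression will assess the difference in medication adherence by group, adjusted for the stratification factors (sex and age) at 12 months". For the rest: "The analysis of the secondary outcomes will be conducted in a similar manner using the appropriate model type", namely logistic, linear or ordinal regression. The covariate set is therefore stated, not left open. None of the sensitivity analyses named there (multiple imputation, per protocol, self-reported adherence where urine data are missing) adds a baseline term.

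On data collection, the Secondary Outcomes section says: "We collected all outcome measures at the baseline and 12-month clinics". Table 1 ticks the urine test and each listed secondary outcome at both visits. Some secondary outcomes are worded as changes, for example "including a change in overall CVD risk score measured by the QRISK2 calculator", but no change-score model is described.

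On allocation, the Randomization section says: "Participants were stratified by age (40-53 years and 54-74 years) and sex". Baseline adherence is not a stratification factor. The eligibility criteria ask for an active prescription, not actual use, and the authors expected some participants not to be taking the statin as directed.

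**The concern.** Each arm is likely to mix people who are and are not taking the statin at entry, and their balance between arms is left to chance. A person's own baseline result is a natural predictor of the 12-month result. A model with only sex and age corrects a baseline gap in adherence only as far as sex and age predict adherence. It also leaves unexplained variation in the comparison that data already in hand could remove. At stake are power on the primary outcome, the width of the intervals on the continuous secondary outcomes, and an avoidable argument about baseline differences when the results are read.

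**Working it through.** **1. The plan's own sample size.** Inputs from Sample Size: 84 per group, 80% power, 5% significance (two-sided assumed), 20% dropout. The section gives a 16-point difference, rates of 91% and 74% (17 points apart), and a 75% control rate in the earlier text-messaging trial. Unpooled formula: n = (1.96 + 0.842)² × [p1(1−p1) + p2(1−p2)] / d².
- 91% v 75%: 7.85 × (0.0819 + 0.1875) / 0.16² = 83 per group (86 with pooled variance). Power at 84 is 79.4%.
- 91% v 74%: 7.85 × (0.0819 + 0.1924) / 0.17² = 75 (78 pooled). Power at 84 is 83.2%.
- Dropout: 84 / 0.8 = 105 per group, 210 in total.

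So 84 fits 91% v 75%. The 16/17-point mismatch does not affect this point, but it explains why the two simulations below start from different unadjusted power.

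**2. Chance imbalance.** Assume 75% baseline adherence and 84 per arm. SE = √(2 × 0.75 × 0.25 / 84) = 0.067, and 1.96 × 0.067 gives ±13 points. For assumed baseline rates of 50% to 74%, the chance of a gap of 10 points or more is about 20% to 14%.

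**3. How much of that reaches the estimate.** The gap is multiplied by the baseline-to-12-month slope. Assumed control-arm adherence in baseline adherers and non-adherers is (0.82, 0.54), (0.87, 0.39) or (0.91, 0.27). The slopes are 0.28, 0.48 and 0.64, and equal phi because both rates are 75%. An extreme 13-point gap then moves the risk difference by 0.131 × 0.28 = 3.7, 0.131 × 0.48 = 6.3 or 0.131 × 0.64 = 8.4 points. These use the control-arm slope. With adherence nearer its ceiling in the intervention arm the slope there is flatter, so they are upper figures.

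**4. Power on the primary outcome, by simulation.** Both simulations use 84 per arm, a constant log-odds treatment effect, and leave sex and age out of both models.

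75% v 91%, baseline adherence 75%, 2,000 runs: power without baseline is 79%, 78% and 79%; with baseline it is 81%, 86% and 92% at phi 0.28, 0.48 and 0.64. The gains are 2, 8 and 13 points.

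74% v 91%, baseline adherence 50%, 60% and 74%, 4,000 runs each, likelihood-ratio test:

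| phi | Without baseline | With baseline | Gain (points) |
|---|---|---|---|
| 0.2 | 84.4–85.8% | 84.8–86.2% | 0.4–0.9 |
| 0.3 | 84.8–85.8% | 86.7–87.8% | 1.6–2.5 |
| 0.4 | 84.8–86.2% | 88.2–89.1% | 2.4–4.0 |
| 0.5 | 84.4–85.3% | 89.8–92.3% | 5.1–7.0 |
| 0.6 (60% and 74% only) | 84.7–85.4% | 92.7–94.2% | 7.3–9.5 |

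Under the null (baseline 74%, phi 0.4) the test rejected in 5.4% of runs without baseline and 5.8% with it, so a small part of the gain may come from that.

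**5. Continuous secondary outcomes.** Relative to a follow-up-only comparison, and with equal variance at both visits, the variance factor is 1 − r² for ANCOVA and 2(1 − r) for an unadjusted change score. Power = Φ(2.80 / √factor − 1.96) where follow-up only has 80%.

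| r | ANCOVA factor | Power | Change factor | Power |
|---|---|---|---|---|
| 0.3 | 0.91 | 83.6% | 1.4 | 65.8% |
| 0.5 | 0.75 | 89.9% | 1.0 | 80.0% |
| 0.7 | 0.51 | 97.5% | 0.6 | 95.1% |

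Since 1 − r² = (1 − r)(1 + r) and 1 + r < 2 whenever r < 1, ANCOVA has the smaller variance even if the changes are meant as change scores.

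**The case against.** The strongest reply is that the planned model is standard and valid. That stands. A reader might infer that leaving out baseline biases the trial or raises its false-positive rate. It does neither: randomisation protects the comparison, and chance imbalance is already part of the variance behind the 95% confidence interval.

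Three further inferences are tempting and not supported.
- That a baseline gap passes in full into the estimate. It is attenuated by the slope, so setting ±13 points directly beside the 16-point target overstates the threat.
- That precision is lost on every outcome. In the planned logistic model, adding baseline raised the median SE of the log odds ratio from 0.46 to 0.48, 0.53 and 0.60 in the three scenarios. Power rises because the conditional odds ratio lies further from 1. The precision gain is on the marginal risk difference, which the article does not plan to report. Nor does every outcome have a listed baseline value: the waist measures named in the abstract have no row in Table 1.
- That the planned multiple imputation would look after missing baselines. It is described for missing outcome data and as a sensitivity analysis, while the primary analysis uses complete data.

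The correlation may also be modest. The article calls the urine test a spot-check (Conclusions), describes statin use as dynamic, and recruited people with raised cholesterol because they were thought more likely to be non-adherent. A 75% baseline rate is therefore only an assumption. At phi 0.2 the gain is under 1 point. For the secondary outcomes, the omission is read from one condensed sentence, and change scores may be intended; against those the advantage at r = 0.7 is only 0.51 v 0.60.

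These replies limit the size of the point. They do not remove it, because the covariates are stated, the data exist, and the expected gain was positive in every scenario.

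**Conclusion.** The point holds as an inexpensive improvement to a stated model, not as an error of validity. On the primary outcome the gain is about 0.5 to 2.5 points of power at phi 0.2 to 0.3 and about 5 to 13 points at phi 0.5 to 0.64. An extreme chance imbalance could move the risk difference by up to roughly 4 to 8 points at phi 0.28 to 0.64, and sex and age would correct only part of that. For continuous secondary outcomes, ANCOVA is more efficient than a follow-up-only analysis for any non-zero correlation, and more efficient than a change score short of perfect correlation. All of this depends on baseline rates and correlations that the documents do not give. The planned sample size does not depend on them.

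**What to change.** Before any comparison by group:
- Add the baseline urine result (detected or not detected) to the primary logistic model with sex and age.
- Add the baseline value to each secondary model where one was collected, using ANCOVA for continuous outcomes.
- Report the standardised (marginal) risk difference with its 95% CI beside the conditional odds ratio, since planning was in percentage points and the odds ratio changes meaning when baseline is added.
- State a rule for missing baseline values, such as a missing indicator or simple baseline imputation, so that nobody with a 12-month result is dropped.
- Keep the sex- and age-adjusted model as a sensitivity analysis.

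The cost is one covariate per model, from data already held. The downsides are the shift to a conditional odds ratio and possible sparse cells. In the three 75% v 91% scenarios, only about 1 to 4 intervention participants who were adherent at baseline would be non-adherent at 12 months, with none in 2%, 11% and 36% of runs, so the plan should say what is done if that cell is empty. The Results section says that follow-up had ended and analysis had not begun. The trial is open and its primary measure has already been changed once (Protocol Amendments), so this change should be dated and documented as made before group results were seen.
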